4.5. DATA COLLECTION

Data of the treatment will discarded, and only the study number will used to code the patient’s measurements. The type of treatment remained unknown to the participating women, and at the end of study period the results will analysed. All participants were given a vaginal exam by the same person, who was blinded to the treatment allocation. The medications were administered in the posterior fornix, and cervical activity was evaluated at baseline and every 3 hours to monitor any change based on the Bishop score.

If the cervical conditions did not change after the treatment application, participants will receive a new dose, without exceeding 4 doses, to facilitate cervical ripening. Once a Bishop score of over 7 will reached, oxytocin will infused in a balanced electrolyte solution beginning with an infusion rate of 2 mIU/min and doubling the dose every 15 minutes. The labour induction time from the first application of medication to the expulsion of the foetus will determined with a digital stopwatch. Each woman's vital signs will verified to determine that she is in stable condition and demonstrated haemodynamic stability as a requirement for the application of a new dose. During this time, the data and medical information will collected on paper and will later entered into a computational database. The participants will remain at rest during the evaluation of adverse effects, such as headache, abdominal pain, pelvic pain, lower back pain, nausea, dizziness, and vomiting. The lack of cervical activity after 4 doses of medication will considered treatment failure.

4.6. PILOT STUDY.

The purpose of conducting the pilot study will be examine the feasibility of an clinical approach study. Our pilot study can be used to evaluate the feasibility of recruitment, randomization, retention of patients and assessment procedures of the novel intervention. Ten women with ultrasonographic diagnosis of fetal death above 20 weeks gestation will be randomly selected to receive the pre-induction treatment based isosorbide dinitrate gel solution or misoprostol gel solution. The time interval between the application of pretreatment, the optimal relaxation of the cervix and conduction of labor will be determined in women in each experimental group. Also, clinical data obtained from these patients will serve to estimate the required sample size. Patients will have access to the best proven therapeutic method identiﬁed by the study.

4.7. STATISTICAL ANALYSIS.

Sample size calculations (Figure 3) will be based on a 97% probability of achieving successful than women undergoing pre-induction therapy with isosorbide dinitrate may reach a score> 7 on the scale of Bishop at 12 hours, and 67% chance for the group of women undergoing pre-treatment with misoprostol (α = 0.05, β = 0.2). Based on these assumptions, at least 30 women will be required for each treatment group. We believe this difference based on the results observed in a preliminary way. Values ​​are presented as mean ± SD. Both IDN and MIS will be evaluated to discern the clinical efficacy using the log rank test and Kaplan-Meier. Hemodynamic data obtained from each experimental group will be analyzed by the Student t test for independent samples. The drug safety will be evaluated based on the data of adverse effects by bivariate analysis (relative risks with 95% confidence interval). The differences in signs and symptoms between groups will be determined by chi-square. P <0.05 will be considered statistically significant. All statistical analyzes will be performed using SPSS for Windows (version 10.0, SPSS Inc., Chicago, USA).

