**2. THEORETICAL ASPECTS**

2.1. BACKGROUND

Foetal death is one of the saddest and most devastating episodes in gynaecology, in which the mother suffers an intense emotional crisis, along with the father and the family. A long delay in labour can increase the risk of anxiety and psychological anguish related to long-term symptoms. Women with little social support are particularly vulnerable to anxiety and postpartum depression.1,2

After the diagnosis of intrauterine foetal death (IUFD), the majority of hospitalised patients opt to deliver the baby within 48 hours.3 However, in women whose pregnancies are not gynaecologically monitored, spontaneous labour within three weeks of foetal death can result in complications for new pregnancies as a consequence of intrauterine infection. The induction of labour in a pregnant woman with an unripe cervical opening can be associated with the failed induction of labour and, invariably, with birth by caesarean section. The pharmacological induction of labour is an obstetric procedure that artificially initiates uterine concentrations that lead to progressive dilation and cervical ripening prior to the administration of intravenous oxytocin.4 For the induction of IUFD, methods of cervical preparation include the vaginal administration of dinoprostone, gemeprost, misoprostol, oxytocin, and progesterone receptor antagonists.5,6 The main problems cited by women during the induction of labour are excessive uterine activity and ineffective labour, which, in association with a history of placenta praevia or uterine surgery, can cause an increase in the risk of uterine rupture.7,8

The therapeutic efficacy and safety of nitric oxide donor drugs has been reported, with isosorbide dinitrate used to induce cervical ripening during the first trimester of gestation.9 Organic nitrates are reductively metabolised to release nitric oxide (NO), which stimulates the activation of soluble guanylyl cyclase (GC). This activation leads to the conversion of GTP into cyclic guanosine monophosphate (cGMP), the second messenger involved in NO mediation.7 The increase in cGMP levels causes the relaxation of the smooth musculature.10-13 In addition, the organic nitrates participate in the endogenous NO production pathway in endothelial cells to maintain vascular tone.14-16 This mechanism has led to an interest in exploring the metabolic activity of NO and medical use of nitrovasodilatory drugs as potential inducers of cervical ripening.

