2.4. JUSTIFICATION

The pharmacological stimulation of cervical ripening in women with late intrauterine death attempts to reduce the number of caesarean sections performed in the medical units of gynecological care. The current pharmacological method for promoting induction of cervical ripening is by using prostaglandins that are generally administered in the posterior fornix of vagina. Evidence has shown histological changes on cervix induced by misoprostol and gemeprost that are similar in proline incorporation by sample protein and the diameter of the collagen fibers in certain tissue biopsies. The action of prostaglandins seems to be in the connective tissue stroma, and evidence of disintegration and dissolution of collagen are supported by the results of intake proline.105 Prostaglandins are not free of adverse effects, maternal and fetal events, mainly because of its stimulatory effect on uterine contractions. After application of prostaglandins for induction of cervical ripening, 5% of women observed uterine hypertonus. During labour, uterine hypertonia is not only painful for the mother, but can also result in fetal distress that often requires emergency caesarean section. Tachysystole and uterine hypertension associated with abnormal patterns of fetal heart rate have also been determine.106 In addition, these drugs have been associated with a number of side effects such as nausea, headache, vomiting, diarrhea, fever, chills, abdominal and vaginal bleeding.

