4.3.1. ELIGIBILITY

Genders Eligible for Study: Female

Accepts Healthy Volunteers: No

CRITERIA

Inclusion Criteria:

- Closed cervix without evidence of cervical dilation or baseline uterine activity.
- A Bishop score of <5, having intact membranes.
- Gestation greater than or equal to 20 weeks established by the date of menstruation or by foetometry and ultrasound-confirmed late IUFD.

Exclusion Criteria:

- Multiple pregnancies.
- IUFD after late foeticide or the management of specific medical conditions associated with an increase in the risk of IUFD.
- Patients with a history of hypertension.
- Women with a history of unexplained antepartum haemorrhage, pelvic dystocia or any another counterindications where medications were used.

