**Main outcome measures:**

The main result of the study will the success rate of foetal expulsion within 15 hours, while the average administration induction interval defined the secondary result.

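### The oxytocin rule in section 4.5 doubles the rate every 15 minutes in both arms, with no maximum, no contraction end-point and no uterine-activity criterion to reduce or stop

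*Protocol*

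**What the plan says.** Section 4.1 makes oxytocin part of both regimens. Section 4.5 starts it at a Bishop score above 7 and then gives the whole dosing rule in one clause: "oxytocin will infused in a balanced electrolyte solution beginning with an infusion rate of 2 mIU/min and doubling the dose every 15 minutes". The next sentence turns to timing labour with a stopwatch. The only other description of the oxytocin dose is in section 2.5.1, which calls it high and gives no figure.

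Section 4.5 contains two limits. The study medication may be given at most four times to ripen the cervix, and the woman must have "demonstrated haemodynamic stability as a requirement for the application of a new dose".

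The background sections describe the relevant hazards. Section 2.1 states: "The main problems cited by women during the induction of labour are excessive uterine activity and ineffective labour". It adds that these, "in association with a history of placenta praevia or uterine surgery, can cause an increase in the risk of uterine rupture". Section 2.4 reports: "After application of prostaglandins for induction of cervical ripening, 5% of women observed uterine hypertonus".

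Among the exclusions in section 4.3.1 is: "Women with a history of unexplained antepartum haemorrhage, pelvic dystocia or any another counterindications where medications were used". The adverse effects listed in sections 4.4 and 4.5 are headache, abdominal, pelvic and lower back pain, nausea, dizziness and vomiting.

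**The concern.** An infusion rule needs a start, a step and an end. This one has the first two. A rate that doubles every 15 minutes rises 16-fold each hour, so the missing end matters far more than it would under a fixed increment. Oxytocin is given to drive contractions, and the protocol itself names excessive uterine activity as a problem of induction and links it to rupture. Staff who follow the protocol exactly are told when to increase the infusion and never when to hold it, lower it or turn it off.

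Blinding adds to the case for a written rule. Under section 4.3 only the pharmacist knows what is in the syringes. The staff running the infusion therefore cannot adjust their caution to whether the woman received a prostaglandin or a nitric oxide donor. A uterine criterion common to both arms works without unblinding.

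What is at stake is the safety of the women in the trial. Dosing limits of this kind belong in a protocol; they are not something usually left to a statistical analysis plan.

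**Working it through.** **Step 1. Does anything in the protocol end the titration?**

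- *Cap of four doses (4.5).* It applies to the ripening medication, not to oxytocin.
- *Haemodynamic check before a new dose (4.5).* The wording matches that for repeating the gel. Even if it were read as covering oxytocin steps, it checks vital signs and not contractions.
- *Three-hourly Bishop assessment (4.5).* It follows the cervix, not uterine activity. Three hours hold 180 / 15 = 12 doublings.
- *Section 2.5.1.* It describes the dose as high, without a number.
- *The 15-hour outcome (4.4).* The main result is "the success rate of foetal expulsion within 15 hours". This is a measurement window, and nothing says that the infusion stops when it closes.

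None of these supplies a maximum rate, a contraction end-point or a criterion to reduce or stop.

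**Step 2. What does the rule give if followed literally?**

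Inputs from section 4.5: start 2 mIU/min, doubled every 15 minutes, so 4 doublings per hour.

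Rate after n doublings = 2 × 2^n mIU/min.

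Cumulative dose up to the n-th doubling = 15 × 2 × (2^n − 1) mIU.

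| Time from start | n | Rate (mIU/min) | Cumulative dose |
| --- | --- | --- | --- |
| 0 | 0 | 2 | 0 |
| 30 min | 2 | 2 × 4 = 8 | 30 × 3 = 90 mIU = 0.09 IU |
| 1 h | 4 | 2 × 16 = 32 | 30 × 15 = 450 mIU = 0.45 IU |
| 2 h | 8 | 2 × 256 = 512 | 30 × 255 = 7,650 mIU = 7.65 IU |

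**Step 3. Does the trial schedule bound it in practice?**

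Section 4.7 takes 12 hours as the time by which the cervix should be ripe. The main outcome is read at 15 hours, which I assume runs from the first application, as the induction time in 4.5 does. A woman who ripens at 12 hours has 15 − 12 = 3 hours left, or 12 doublings. The literal rate is then 2 × 4,096 = 8,192 mIU/min. A woman who ripens sooner has longer. The schedule therefore sets no useful limit.

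**Step 4. Does any statistical quantity depend on this?**

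No. The sample size in 4.7 rests on a Bishop score above 7, which is reached before oxytocin starts. The infusion rule is not split by arm.

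**The case against.** The infusion is run in the obstetrics department of a perinatal institute, with vital signs checked, and no clinician would double oxytocin to 512 mIU/min. The high dose is a deliberate choice. The documents give no safe maximum, so they cannot show at which step harm begins. Some pages, the figures and any accompanying tables are not available.

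Much of this stands. The literal rates show only that the rule has no bound, not what any woman would receive. But relying on staff to depart from the written rule is not a safeguard, and choosing a high dose does not say where it ends. The infusion sentence is complete and points to no other source; the missing material could still hold a limit.

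A reader might draw several stronger conclusions that the documents do not support:

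- *That the number of women needing a stop rule can be computed.* With 67% of 30 misoprostol women ripening, 30 × 0.67 is about 20, and 5% of 20 is one case. But the 5% in section 2.4 is a background figure for hypertonus after prostaglandins. It is not a rate under oxytocin, nor one for 100 mcg misoprostol after fetal death. It cannot be carried to the isosorbide arm, since 2.4 describes nitric oxide as relaxing the myometrium. Applying it to all 30 women would also count those who never ripen and, under 4.5, get no infusion.
- *That the protocol expects excessive uterine activity in this trial.* Section 2.1 is general background. The hypothesis in 2.5.2 names headache and pelvic pain as the main anticipated effects.
- *That women with prior uterine surgery or placenta praevia will be enrolled.* Neither history is named in 4.3.1, but the loosely worded contraindication clause may cover both.
- *That uterine events will go uncollected.* The lists are not exhaustive: 4.4 omits even the Bishop score, and the list in 4.5 is given as examples. They show only that these items are not listed.
- *That the comparison between arms is biased.* Expulsion comes after oxytocin, but the rule is the same in both arms and the staff are blinded.

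**Conclusion.** The point holds as a gap in the intervention and safety specification. Section 4.5 gives an escalation rule with no end, and nothing in the available text supplies one. Its size is best put as a literal reading: 32 mIU/min after 1 hour and 512 mIU/min after 2 hours, neither being an expected exposure. The documents give no rate of excessive uterine activity under oxytocin, so the number of women affected cannot be stated.

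The conclusion assumes that the parts of the protocol not available do not contain a limit. It rests on maternal safety alone and has no consequence for any statistic or for the comparison between arms. For that reason, and because the ceiling itself is a clinical value for the obstetric lead to set, this should be fixed but is not a fault that invalidates the design.

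**What to change.** Replace the infusion sentence in section 4.5, identically for both arms, with a rule along these lines: start at 2 mIU/min and double every 15 minutes only until adequate contractions are established or a stated maximum rate is reached, whichever comes first; do not start the infusion, or reduce or stop it, in the presence of tachysystole or hypertonus. The obstetric lead sets the maximum rate and defines adequate contractions, tachysystole and hypertonus. All of these should be written into the protocol.

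Add to the variables in 4.4: peak oxytocin rate, any tachysystole or hypertonus, and any reduction or stop of the infusion.

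The cost is a short amendment and a few case-report fields. It needs no extra patients, no procedures beyond bedside observation of labour, and no change to the sample size or the planned tests.

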2.2. PROBLEM STATEMENT

The pre-induction of labor is an obstetrical procedure that is performed on women to provide a vaginal delivery in those with fetal death. The real benefit of the procedure is to avoid the risk of systemic infection in patients for performing a cesarean section. At present, the treatment indicated to start induction of labor has been established with the use of drugs like prostaglandins. Misoprostol and Dinoprostone have been widely administered during the last decade for inexpensive, easy to administer, effective and safe. However, Misoprostol, like other drug analogs is associated with adverse effects on the mother, especially abdominal pain, nausea, and vaginal bleeding leading to tachycardia that pregnancy is resolved through the abdomen emergency. It is also known that the frequency and intensity of these side effects are increased if the time interval in the pre-induction is prolonged.

At National Institute of Perinatology, the number of fetal deaths over 20 weeks of gestation has increased gradually. During the course of 1998 to 2006, mortality has increased from 95 cases to 211 in the period, with a fetal mortality rate of 38.6 per 1000 births for 2006. The procedures are often used to address labour in women with fetal death, to mention just a few examples, such as caesarean section or use of oxytocin without evidence of cervical ripening can contribute to increased maternal morbidity. In medical practice, using isosorbide dinitrate gel solution prior to induction of cervical dilation might reduce damage, economic cost of surgical procedures and risks to the health of the mother.

2.3. BIBLIOGRAPHIC HISTORY.

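### Excessive uterine activity, hypertonus and tachysystole are named as hazards, but no uterine-activity item is listed after entry and the gel and oxytocin rules in section 4.5 contain no contraction criterion

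*Protocol*

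**What the plan says.** **The hazard.** Section 2.1: "The main problems cited by women during the induction of labour are excessive uterine activity and ineffective labour". Section 2.4 explains the case against prostaglandins in the same terms: "Prostaglandins are not free of adverse effects, maternal and fetal events, mainly because of its stimulatory effect on uterine contractions". It gives a rate, "After application of prostaglandins for induction of cervical ripening, 5% of women observed uterine hypertonus", calls hypertonus painful for the mother, and also names tachysystole. Section 2.2 says that misoprostol "is associated with adverse effects on the mother, especially abdominal pain, nausea, and vaginal bleeding".

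**What is recorded.** Absence of uterine activity is an entry requirement (4.3.1). After entry, the objective (2.5.1) lists vital signs and symptoms, including abdominal pain and vaginal bleeding. The adverse-effects checklist in 4.4 has seven symptoms: headache, abdominal, pelvic and lower back pain, nausea, dizziness and vomiting. Section 4.5 repeats these seven. Its repeated examination concerns the cervix: "cervical activity was evaluated at baseline and every 3 hours to monitor any change based on the Bishop score".

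**The dosing rules, all in 4.5.**
- Gel, trigger and limit: "If the cervical conditions did not change after the treatment application, participants will receive a new dose, without exceeding 4 doses".
- Gel, safety condition: vital signs are "verified to determine that she is in stable condition and demonstrated haemodynamic stability as a requirement for the application of a new dose".
- Oxytocin, once the Bishop score exceeds 7: "oxytocin will infused in a balanced electrolyte solution beginning with an infusion rate of 2 mIU/min and doubling the dose every 15 minutes".

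**The concern.** The safety argument for the nitrate in sections 2.4 and 2.5.1 turns largely on uterine stimulation: prostaglandins provoke contractions, whereas nitric oxide relaxes the myometrium. One would expect the adverse-effect comparison to measure that directly and the dosing rules to respond to it. Neither is written down.

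Two things are at stake. First, interpretation. Section 2.5.2 predicts mainly pelvic pain on misoprostol. Pain may come from overstimulation or from the ordinary contractions of an effective induction, and no listed item separates the two. Second, the women's safety. The protocol gives staff an explicit condition for redosing but builds it on vital signs. Because staff are blinded, they cannot adjust their vigilance to the drug given, so a written rule common to both arms matters more than it would in an open trial.

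Dosing rules and the list of safety items belong in a protocol; this is not detail that would wait for an analysis plan.

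**Working it through.** **1. Hazards against recorded items**

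| Item | Named as a problem | Recorded after entry |
|---|---|---|
| Excessive uterine activity | 2.1 | not listed |
| Hypertonus | 2.4 (5%) | not listed |
| Tachysystole | 2.4 | not listed |
| Abdominal pain | 2.2 | 2.5.1, 4.4, 4.5 |
| Nausea | 2.2 | 2.5.1, 4.4, 4.5 |
| Vaginal bleeding | 2.2 | 2.5.1 |

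The misoprostol effects in 2.2 are largely covered, so the gap concerns uterine activity only. Two entries could be mistaken for coverage. Uterine size in 4.4 is a dimension, and the cervical activity in 4.5 is the Bishop score.

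**2. The dosing rules applied to a woman with hypertonus**

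- Gel: suppose her cervix is unchanged, she has had fewer than four doses, and her vital signs are normal. The group headed haemodynamic stability in 4.4 consists of heart rate, respiratory rate, temperature and blood pressure. She meets every written condition for another dose.
- Oxytocin: the rule gives a trigger, a starting rate of 2 mIU/min and a step (doubling every 15 minutes). It gives no contraction target, hold, stop or maximum.

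**3. The protocol's own figure**

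The only design calculation is the 30 women per group in 4.7 (97% against 67%, α 0.05, power 80%). With a two-sided test, n = [1.96·√(2·0.82·0.18) + 0.842·√(0.97·0.03 + 0.67·0.33)]² / 0.30², which gives 25. With continuity correction it is 31, close to the stated 30. Below, 30 serves only as a denominator; the point does not depend on how it was derived.

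**4. How many cases the item might capture**

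Assumption: the 5% in 2.4, a figure for prostaglandins as a class, applies to the misoprostol arm. The protocol gives no misoprostol-specific rate, so a range of 2% to 10% is also shown.

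- Expected women = 30 × p
- Chance of at least one = 1 − (1 − p)^30

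| Assumed rate p | Expected of 30 | Chance of at least one |
|---|---|---|
| 2% | 0.6 | 45% |
| 5% | 1.5 | 1 − 0.95^30 = 79% |
| 10% | 3.0 | 96% |

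**5. What such counts could show**

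Exact (Clopper-Pearson) 95% limits:
- 0 of 30: upper limit 1 − 0.025^(1/30) = 11.6%
- 2 of 30: 0.8% to 22.1%

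The item would describe the arms, not test them.

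**The case against.** **The lists are open.** Sections 2.5.1 and 4.5 both introduce their adverse effects with the words such as, and 4.5 says that medical information is collected on paper. A reader might infer from the gap that overstimulation could not be recorded at all; the text does not support that. What stands is that an open list does not ensure defined and equal recording in both arms.

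**There is a bedside check before every gel dose.** A stable condition is required. However, 4.5 ties it to vital signs and haemodynamics, so it is not a contraction rule. Equally, the protocol does not say that clinicians would in fact redose a woman in hypertonus.

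**Extrapolating the rules exaggerates exposure.** A reader might count every possible redosing decision, or run the doubling on for hours to extreme oxytocin rates. Neither is a realistic exposure. Section 2.5.2 expects most women to ripen by 12 hours, and a starting rate with a step size is not a forecast. The objection is accepted: the point is the missing limit, not a projected dose.

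**The harm is narrower here.** The foetal consequences in 2.4 do not apply after foetal death. Maternal pain is recorded in three forms, and bleeding is named in the objective. The rupture risk in 2.1 is linked to previous placenta praevia or uterine surgery, and 4.3.1 excludes contraindications in general terms. This limits the seriousness but does not supply the missing item or rule.

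**No stated analysis fails.** This is correct. Section 2.5.2 predicts only which symptoms women will report.

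**Conclusion.** The point holds in limited form. The protocol uses uterine overstimulation to justify the trial, lists no item that records it after entry, and writes gel and oxytocin rules that, taken literally, allow further stimulation while it is present. Overstimulation could surface only through abdominal, pelvic or back pain, bleeding, or an unlisted entry.

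The size is modest: about 1.5 of 30 misoprostol women if the class figure applies, 0.6 to 3.0 over the assumed range. The protocol gives no rate for tachysystole, for events during oxytocin, or for redosing during hypertonus.

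A reader might infer that the efficacy result is compromised. It is not: the hypotheses in 2.5.2 and the 15-hour expulsion outcome in 4.4 stand as defined. Severity: consider. Figures are missing from the text at hand, but from their description they are unlikely to hold a contraction rule.

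**What to change.** **Record it.** Add hypertonus/tachysystole (yes/no) to the adverse-effects checklist in 4.4, with a definition written into the protocol and identical for both arms. Complete it at each existing 3-hourly blinded examination and whenever the event is noticed during oxytocin. Report it by arm as counts with exact 95% intervals and no test. These are partly spot checks, so 0 of 30 should not be read as absence.

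**Act on it.** Add to 4.5, for both arms: 'While hypertonus or tachysystole is present, the next gel dose is withheld and oxytocin is not increased; oxytocin is reduced or stopped if the condition persists.' State the site's usual maximum oxytocin rate.

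**Account for it.** Log withheld doses by arm, and keep these women in their randomised arm for the 15-hour outcome.

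**Cost.** There is a little more bedside recording, including during oxytocin. The real downside is that holds may be more frequent on misoprostol and could lower its 15-hour success, which would favour the nitrate. A reader might take the 5% in 2.4 as a ceiling on that effect. It is not one: it covers hypertonus only, is a class figure for prostaglandin ripening, and leaves out tachysystole and holds during oxytocin. The effect cannot be bounded from the protocol, but the log would make it visible.
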